**6. CRITERIA FOR DISCONTINUATION/WITHDRAWAL OF INFORMED CONSENT**

Patients may be discontinued from trial treatment and assessments at any time, at the discretion of the investigator(s). Specific reasons for discontinuing a patient from study treatment are

- objective progression of disease
- patient lost to follow-up (i.e., dropouts)
- adverse events
- protocol non-compliance
- withdrawal of consent

If the reason for withdrawal from the trial is the death of the patient, the two options for categorizing withdrawal are either progressive disease or an adverse event (AE; more than one AE may be documented as a reason for withdrawal). Only one event will be captured as the cause of death. Note that death is an outcome and not an AE.

All deaths that occur within the trial period or within 30 days after administration of the last dose of radiation therapy must be reported primarily for the purposes of serious adverse event (SAE) reporting; however, deaths due unequivocally to progression are not SAEs.

All trial treatment-related toxicities and SAEs must be followed up until resolution.

All patients who have new or worsening grade 3 or 4 laboratory values (Common Terminology Criteria for Adverse Events (CTCAE)) at the time of withdrawal must have additional testing performed, and the results must be recorded in the patients’ medical records. These patients should be followed until the laboratory values have returned to CTCAE grade 1 or 2, or until 30 days after the date of withdrawal (whichever comes first), unless these values are not likely to improve because of the underlying disease. In these cases, the investigators must record their opinions in the patients’ medical records. Laboratory abnormalities should not be reported as adverse events unless any criterion for an SAE is fulfilled, the laboratory abnormality causes the patient to discontinue from the study, or the investigator insists the abnormality should be reported as an AE.

After withdrawal from treatment, unless the patient withdraws consent, follow-up should continue for determination of adverse events, progression-free survival, and overall survival.

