9.3 Phase I and II Maintenance dose: will be 50 mg PO QD

9.4 Schedule:

- One days 1-28, Sutent will be taken p.o. in the morning
- Two weeks after completion of any chemotherapy, maintenance Sutent in 6 week cycles (consisting of Sutent 50 mg PO QD weeks 1-4 followed by no treatment weeks 5-6) until progression or death

9.5 Formulation and Packaging: SU011248 is a small molecule inhibitor of the receptor tyrosine kinases VEGFR, PDGFR, KIT, and FLT3. In this clinical trial, study medication of SU011248 refers to the investigational agent SU011248 L-malate. Sunitinib L-malate salt will be supplied as hard gelatin capsules containing 12.5-mg, 25-mg, and 50-mg equivalents of Sunitinib malate free base, in bottles containing 30 capsules each."

9.6 Storage:Store at 25º C (*77º F*); excursions permitted to 15-30º C (*59-86º F*).

9.7 Adverse Effects: Data regarding the safety of Sutent are largely from a Phase III randomized trial of 304 patients with metastatic GI stromal tumors following imatinib failure who were treated with Sutent vs. placebo and 169 patients with metastatic renal cell carcinoma treated on phase II trails (32, 33).

Cardiac: Left Ventricular Dysfunction – The incidence of decreased left ventricular ejection fraction to below the lower limit of normal is 11-15% with Sutent vs. 3% for placebo. Over 40% of patients recover left ventricular ejection fraction without intervention. Only 1% of patients suffered grade 3 left ventricular systolic toxicity. Sutent should be discontinued in the presence of clinical congestive heart failure. The Sutent dose should be reduced in all patients without clinical congestive heart failure but with an ejection fraction of <50% and a drop of over 20% from baseline.

Hemorrhagic Events: Bleeding occurred in 18 to 26% of patients receiving Sutent vs. 17% for placebo with epistaxis being the most common hemorrhagic event. The incidence of Grade 3-4 bleeding is 1 to 7% among patients receiving Sutent vs. 9% for placebo. However, fatal pulmonary hemorrhage was noted in two patients with non-small cell lung cancer. Bleeding events, including fatal GI bleeding, has been noted in patients within 30 days of completing Sutent. Although there is no specific contraindication for concurrent anticoagulants, patients requiring continued Coumadin, lovenox, heparin, NSAIDs, aspirin, plavix or similar drugs will be excluded from this study (12/16/09).

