9.10 Dose Modifications for Sutent(Applies only to phase II)

Dose modification of Sutent can be secondary to any grade 3 toxicity related to Sutent according to the judgment of the treating physician. When toxicities eliciting dose modification occur, Sutent will be temporarily discontinued but restarted at the next lower dose level when the toxicity has resolved to grade 2 or lower. In the event of hospitalization for reasons other than drug toxicity, patients should be directed to continue trial drug at the discretion of their physician. The principal investigator should be notified immediately of any compliance issues that arise in the course of the trial. If a patient still experiences dose-modifying toxicities despite drug holiday and reduced dose schedule, the patient, if benefiting from treatment, should stop receiving Sutent and continue radiation.

The following toxicities, in addition to any other toxicity as judged by the treating physician, merit temporary discontinuation should be considered dose-limiting toxicity:

1. Any CTC grade 3 or 4 non-hematopoietic adverse event that the investigator considers consistent with a drug-related toxicity;

2. Any CTC grade 4 hematopoietic adverse event that the investigator considers consistent with a drug-related toxicity;

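### Section 9.10's phase II hold-and-restart rule makes no exception for clinical heart failure or severe hypertension, for which Section 9.7 says to discontinue Sutent

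*Protocol*

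**What the plan says.** Two parts of Section 9 of the protocol tell the physician what to do about serious Sutent toxicity.

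**Section 9.10 (dose modifications, phase II only).**
- Trigger: "Dose modification of Sutent can be secondary to any grade 3 toxicity related to Sutent according to the judgment of the treating physician".
- Action once triggered: "Sutent will be temporarily discontinued but restarted at the next lower dose level when the toxicity has resolved to grade 2 or lower".
- Events listed as meriting temporary discontinuation include: "Any CTC grade 3 or 4 non-hematopoietic adverse event that the investigator considers consistent with a drug-related toxicity". Drug-related grade 4 hematopoietic events are listed too, and the physician may add others.
- Sutent is stopped for good, with radiation continuing, only if dose-modifying toxicity persists after both the drug holiday and the reduced dose.

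**Section 9.7 (adverse effects, not limited to either phase).**
- Clinical heart failure: "Sutent should be discontinued in the presence of clinical congestive heart failure".
- Ejection fraction below 50% with a fall of more than 20% from baseline, but no clinical heart failure: reduce the dose.
- Severe hypertension, defined as systolic above 200 or diastolic above 110: discontinue.

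Section 9.3 sets maintenance at 50 mg daily in both phases and names no exception.

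**The concern.** Section 9.10 is where a treating physician would look when a phase II patient has a serious drug-related event. It describes its events by grade and attribution, not by organ, so drug-related heart failure of grade 3 or 4 is covered. The instruction found there is to hold and then restart one level lower. The instruction in 9.7 for the same event is to discontinue. Two physicians, each following the protocol, could therefore treat the same patient differently, and one of them would give the drug again after drug-related heart failure. Maintenance cycles run until progression or death, so the re-exposure need not be short.

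What is at stake is the safety of an occasional patient and uniform handling of a serious cardiac event.

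**Working it through.** No arithmetic applies. The check is to follow one event through each section.

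**Step 1: does 9.10 reach heart failure?** The list covers any non-hematopoietic event of grade 3 or 4 that the investigator attributes to the drug. Drug-related heart failure of those grades meets that description, and no cardiac event is carved out. Heart failure that never exceeds grade 2, or is not attributed to Sutent, is outside the list.

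**Step 2: what does each section instruct?**

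| Event | Section 9.7 | Section 9.10 as written (phase II) |
|---|---|---|
| Ejection-fraction fall, no clinical heart failure | Reduce dose | If grade 3 or 4 and drug-related: hold, restart one level lower |
| Clinical heart failure | Discontinue | If grade 3 or 4 and drug-related: hold, restart one level lower at grade 2 or below |
| Severe hypertension | Discontinue | If grade 3 or 4 and drug-related: hold, restart one level lower at grade 2 or below |

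Section 9.7 has two cardiac tiers, reduction and discontinuation. Applying 9.10 to heart failure removes the difference between them.

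**Step 3: can the two be reconciled?** Section 9.7 ties discontinuation to the presence of heart failure and does not say whether it is permanent.
- If it means only while heart failure is present, the sections are compatible once the condition has fully cleared. But 9.10 restarts at grade 2 or lower, not at resolution, and the protocol does not say whether residual grade 2 heart failure still counts as present.
- If it means permanently, 9.10's restart is inconsistent with it.

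**Step 4: does another section settle it?**
- Section 5, exclusion 3, bars any history of clinically significant heart failure, but governs entry only.
- Section 6 lists adverse events among the reasons for stopping treatment and gives the investigator discretion to stop at any time. It permits a stop and does not require one.
- Section 9.10 leaves the decision to modify the dose to the physician, but states the restart that follows as what will happen.
- Neither 9.7 nor 9.10 refers to the other or states precedence.

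**Step 5: can a frequency be given?** No. The cardiac figures in 9.7 are for other events. One is a single grade of systolic dysfunction and leaves out grade 4, which 9.10 includes: "Only 1% of patients suffered grade 3 left ventricular systolic toxicity". Another is a laboratory-type decline, with 11-15% on Sutent against 3% on placebo. The last is recovery of ejection fraction, which is not recovery from heart failure: "Over 40% of patients recover left ventricular ejection fraction without intervention". Multiplying them together would not estimate how often a restart question arises.

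**The case against.** The strongest reply is that the protocol already deals with heart failure. Section 9.7 gives an instruction specific to it and, in the same paragraph, confines dose reduction to patients without it. Section 9.10 concerns toxicities that call for dose modification; an event for which the drug is discontinued need never enter that pathway. A specific rule is ordinarily read as overriding a general one, especially within the same section. The 9.10 trigger is permissive, so no physician is forced to hold and restart, and Section 6 allows withdrawal at any time. On this view only a cross-reference is missing.

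Much of this stands. It rules out the reading that the two sections flatly contradict each other or that re-challenge after heart failure is intended. A reader might infer either, but neither section says so, and 9.7 remains in force. The reply does not remove the gap: precedence has to be inferred, 9.10's list takes in the event without exception, and discretion to stop is not an instruction to stop.

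A reader might also infer that 9.7 means permanent discontinuation. The text does not say that; whether restart is ever acceptable is a clinical choice it leaves open.

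**Conclusion.** The point holds as a minor patient-safety inconsistency. Section 9.10 applies hold-and-restart to drug-related grade 3 or 4 non-hematopoietic toxicity without excepting clinical heart failure or severe hypertension, while 9.7 says to discontinue for both. A sensible reader may let 9.7 control, but the protocol does not say so.

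The conclusion rests on two readings of the text: that heart failure, or severe hypertension, is graded 3 or 4 and attributed to Sutent, so that 9.10 applies; and that the physician chooses to modify the dose under that section. It is confined to phase II. Its size cannot be expressed as a probability from this protocol. Nothing in the endpoint definitions, the power statement or the stated α depends on it.

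**What to change.** Add to Section 9.10: *The hold-and-restart rule does not apply to clinical congestive heart failure or severe hypertension; these are managed under Section 9.7 (discontinue Sutent, including maintenance).*

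In Section 9.7, the sponsor should state whether discontinuation for these two events is permanent or, if restart is allowed, on what conditions. That is the sponsor's clinical decision; this review does not prescribe the answer.

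The cost is one added sentence in 9.10 and a short clarification in 9.7, with no extra patients, visits or procedures. The downside is that a rare patient who recovers may lose further Sutent.

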**10. PHASE I DOSE ESCALATION RULES**

- Both radiation dose and Sutent dose will be escalated in 5 dose levels.

**Table 1. Phase I Dose Levels**

| **Dose Level** | **Radiation Dose** | **Sutent Dose** |
| --- | --- | --- |
| 1 | 40 Gy in 10 fractions | 25 mg PO QD |
| 2 | 40 Gy in 10 fractions | 37.5 mg PO QD |
| 3 | 50 Gy in 10 fractions | 37.5 mg PO QD |
| 4 | 50 Gy in 10 fractions | 50 mg PO QD |
| 5 | 60 Gy in 10 fractions | 50 mg PO QD |

.

Phase I dose escalation will proceed according to a “3+3” design. After 3 patients have been treated on each dose level, they will be followed for at least 30 days. If 0 of 3 patients have DLTs, the dose will be escalated to the next dose level. If ≥2 of 3 patients have DLTs, dose escalation will be terminated and the next lowest dose level will be declared the maximal tolerated dose for Phase II evaluation. If 1 of 3 patients has a DLT, then three more patients will be treated at the same dose level and if the incidence of DLT among six patients is < 2 of 6, the dose will be escalated to the next level for that site.

- Grades 3-5 non-hematological toxicities (excluding nausea, vomiting, and alopecia) and Grade 4-5 hematological toxicities will be referred to as dose limiting toxicities (DLT).
  - Esophagitis and mucositis are very common side effects with radiation therapy and grade 3 side effects can be seen after palliative courses of radiotherapy. Therefore, grade 3 mucositis or esophagitis lasting ≤ 7 days will **not** be considered a DLT. If the grade 3 mucositis or esophagitis lasts > 7 days, it will then be considered a DLT.
- The recommended phase II dose will be 1 dose level below the defined MTD or at the maximum tested dose if the MTD has not been reached.

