**Statistical analysis:**

*Phase I: Feasibility and toxicity.* Patients will receive concurrent treatment with extracranial radiosurgery and Sutent. Both the radiation dose and Sutent dose will be escalated as the trial progresses from Levels 1 through 5 as shown in Table 1. The starting radiation dose is 40 Gy in 10 fractions and the starting Sutent dose is 25 mg PO QD. The dose escalation strategy is as follows: The trial will start with dose level 1. At each level, 3 patients will be treated and their toxicities will be assessed. If no patients experience dose limiting toxicity, the trial will proceed to the next dose level. If 1 patient develops unexpected acute toxicity at any dose level, an additional 3 patients will be treated at that dose level. If ≥2 patients experience unexpected toxicity, the previous dose level will be declared the maximal tolerated dose for Phase II evaluation

*Phase II (Includes 3 to 6 patients from Phase I MTD):* The median progression free survival with optimal chemotherapy alone for the 4 most common tumor types (lung, breast, prostate and colorectal) ranges from 2.2 to 10.6 months, depending on primary tumor site and degree of pretreatment. Therefore, we will assume a median time to progression of 6.4 months (standard deviation 3.2 months) with chemotherapy alone. Using the data from this trial, response rates will be estimated and Kaplan-Meier curves generated for progression-free and overall survival (1). With 38 patients for the phase II portion, this study has 87% power (α=0.05) to detect a 25% increase in time to progression. Also the 2 year freedom from progression is <5% with chemotherapy therapy and this study has 70% power (α=0.05) to demonstrate a 10% absolute increase in 2 year progression-free survival.

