11. Radiation is to be delivered to each site over 10 fractions separated by at least 16 hours. Up to 5 sites may be treated. **(Added 7/27/06)** For patients with 3 to 5 sites of disease, it may be difficult to treat all sites of disease during one day. For these patients, an acceptable variant is to treat all 2 to 3 sites during days 8 to 19 and to treat the remaining sites on days 20 to 33. For these patients only, concurrent Sutent will continue until day 42.
12. Radiation Doses (Phase I): A phase I escalation of doses will be performed in order to determine in MTD in Gy

Doses of radiation will increase as follows in order to determine the MTD of radiation in combination with Sutent:

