**16. STATISTICAL CONSIDERATIONS**

- Phase I: The primary objectives are to determine the maximum tolerated dose (MTD) and dose limiting toxicity (DLT) of extracranial stereotactic radiation therapy in combination with Sutent when given to all sites of involved disease in patients with metastatic cancer.
- For dose escalation purposes, the major endpoint will be dose-limiting toxicity occurring within 30 days after the start of radiation therapy.
- Dose limiting toxicity is defined as follows: Grade 3-5 non-hematological toxicities (excluding nausea, vomiting, and alopecia) and Grade 4-5 hematological toxicities.
  - Esophagitis and mucositis are very common side effects with radiation therapy and grade 3 side effects can be seen after palliative courses of radiotherapy. Therefore, grade 3 mucositis or esophagitis lasting ≤ 7 days will not be considered a DLT. If the grade 3 mucositis or esophagitis lasts > 7 days, it will then be considered a DLT.
- The MTD for a specific area will be exceeded if 2 or more patients out of 6 (or a third or more) with disease at that site experience DLT at that dose. The dose immediately below will be recommended for further study.
- Phase II: *(Includes 3 to 6 patients from Phase I MTD):* The median progression free survival with optimal chemotherapy alone for the 4 most common tumor types (lung, breast, prostate and colorectal) ranges from 2.2 to 10.6 months, depending on primary tumor site and degree of pretreatment. Therefore, we will assume a median time to progression of 6.4 months (standard deviation 3.2 months) with chemotherapy alone. With 38 patients, this study has 87% power (α=0.05) to detect a 25% increase in time to progression. Also the 2 year freedom from progression is <5% with chemotherapy therapy and this study has 70% power (α=0.05) to demonstrate a 10% absolute increase in 2 year progression-free survival.
  - All patients included in the study will be assessed for response to treatment, even if there are major protocol treatment deviations or if they are ineligible (intent-to-treat population). Criteria described in Section 10 will be used to assign each patient to one of the following response categories: 1) complete response, 2) partial response, 3) stable disease, 4) progressive disease, 5) early death from malignant disease, 6) early death from toxicity, 7) early death because of other cause, or 8) unknown (not assessable, insufficient data).

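### The 3+3 rule counts patients treated and followed for 30 days, with no minimum exposure and no replacement; for staged radiation the DLT window also closes before concurrent Sutent ends

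*Protocol*

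**What the plan says.** The counting rule appears twice. Section 10, below the dose-level table, says "After 3 patients have been treated on each dose level, they will be followed for at least 30 days". No DLT in three patients opens the next level. One DLT adds three more patients, and fewer than two DLTs in six opens the next level. The synopsis (Statistical analysis) says "At each level, 3 patients will be treated and their toxicities will be assessed" and, on expansion, "If 1 patient develops unexpected acute toxicity at any dose level, an additional 3 patients will be treated at that dose level".

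Section 16 fixes the outcome being counted: "the major endpoint will be dose-limiting toxicity occurring within 30 days after the start of radiation therapy". Radiation starts on day 8 and Sutent is taken on days 1-28 (synopsis, Treatment Plan).

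Section 6 allows treatment to be stopped at any time at the investigator's discretion. Its listed reasons include progression, loss to follow-up, non-compliance and withdrawal of consent. Unless consent is withdrawn, follow-up for adverse events continues after treatment stops. The section does not say how such a patient counts in a phase I cohort.

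Section 8.1, item 11, allows patients with three to five sites to have some sites treated on days 8-19 and the rest on days 20-33. It adds: "For these patients only, concurrent Sutent will continue until day 42".

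**The concern.** The MTD and the recommended phase II dose are the phase I primary objective, and the synopsis states that there are no clinical data on the combination. The 3+3 rule is informative only if each counted patient had enough of the regimen to show its toxicity. A patient who stops after a few fractions, remains under observation and has no DLT supplies little evidence of safety, yet can fill one of the three places. The error has one direction: it can raise the chance of escalation but not lower it.

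The first people exposed to this are those treated at the next phase I level. For phase II, the synopsis (Treatment Plan) and Section 10 put the recommended dose one level below the MTD, which softens the effect. That step-down does not apply if level 5 is passed, and Sections 9.2 and 9.9 give phase II the MTD itself.

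The staged-radiation variant raises a second, separate question: whether the DLT window covers the whole concurrent course.

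**Working it through.** **1. Inputs.** The escalation rule is from Section 10. The protocol states no operating characteristics for phase I, so there is no stated figure to reproduce. It also gives no early-stop rate and no expected DLT rates. The values below are assumptions: early stops of 5% or 10% per patient, true DLT rates of 30% to 50%, and early stoppers who carry either no DLT risk or half of it.

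**2. Chance of passing one level with full exposure.** With DLT rate p and q = 1 − p:

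F(p) = q³ + 3pq² × q³

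At p = 0.40: 0.216 + 0.432 × 0.216 = 0.309.

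**3. With early stoppers counted as DLT-free.** If a share s stop early and keep a share h of the DLT risk, the effective rate is p × (1 − s(1 − h)). For p = 0.40, s = 10%, h = 0 this is 0.36, and F(0.36) = 0.262 + 0.442 × 0.262 = 0.378.

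| True DLT rate | No early stops | 5%, half risk | 5%, no risk (same as 10%, half risk) | 10%, no risk |
|---|---|---|---|---|
| 30% | 0.494 | 0.510 | 0.525 | 0.557 |
| 40% | 0.309 | 0.326 | 0.343 | 0.378 |

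At 40% the rise is 1.7 to 6.9 points. At a true rate of 50% with no residual risk, the chance goes from 0.172 to 0.202 (5%) or 0.234 (10%). All these figures treat every early stopper as followed for 30 days and counted, so they are upper values for their inputs.

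**4. Given that it happens.** Suppose exactly one of the first three patients is effectively unexposed and is counted. The chance of passing is then q² + 2pq × q³. At 40% this is 0.36 + 0.48 × 0.216 = 0.464, against 0.309. The chance of at least one early stopper among three is 1 − 0.95³ = 14% at a 5% stop rate and 1 − 0.90³ = 27% at 10%.

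**5. Window for the staged variant.** Radiation starts on day 8, so the Section 16 window ends on day 8 + 30 = day 38. On the standard schedule Sutent ends on day 28 and is covered. Under the variant radiation can run to day 33 and Sutent to day 42, so the last four days of concurrent Sutent (days 39-42) fall outside the window.

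**The case against.** Five arguments deserve an answer.

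*The follow-up condition already excludes some stoppers.* This is correct. A reader might infer that any patient who leaves early, including one lost or withdrawing consent, counts as DLT-free. Section 10 does not support that: such a patient has not been followed for 30 days. What remains for them is only that no replacement is provided.

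*Progression will rarely stop treatment in time.* This is largely right. The first scheduled imaging is 4-6 weeks after radiation. With the last fraction on day 19, that is about day 47 to day 61, after Sutent ends and the window closes. Section 4 also requires life expectancy above three months. Clinically evident progression, non-compliance and discretionary stops remain possible.

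*Treated on a dose level naturally means the full course in the table.* This is a fair reading, and a careful investigator might apply it. But the protocol does not say so, and does not say what happens if fewer than three complete the course. The biweekly review in Appendix 3 makes early stops visible without giving a counting rule.

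*Toxicity-driven stops.* A reader might infer that these escape the rule too, and that every patient under-exposed because of toxicity should be scored as a DLT. The documents do not support going that far. The synopsis trigger in "If 1 patient develops unexpected acute toxicity at any dose level, an additional 3 patients will be treated at that dose level" may catch some of them. Section 9.10 does say of certain toxicities "in addition to any other toxicity as judged by the treating physician, merit temporary discontinuation should be considered dose-limiting toxicity", but its heading restricts it to phase II. Section 10 deliberately leaves out nausea, vomiting and grade 3 mucositis or esophagitis lasting up to seven days, and an automatic DLT would override that.

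*Follow-up of at least 30 days after treatment could run past day 42.* It could, but Section 16 defines which toxicities count for escalation, and its limit runs from the start of radiation.

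Nor can this be left to a statistical analysis plan. The count decides during the trial whether the next patients receive a higher dose, and the protocol itself fixes that rule.

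**Conclusion.** The gap is real but narrow. As written, a patient who stops radiation or Sutent early for a non-toxicity reason and stays in follow-up can count toward 0 of 3, and nothing provides for replacing patients who cannot be assessed. The bias runs only toward escalation.

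Its size is not known. With an assumed 5-10% early stops it is about 2 to 7 points on a 31% chance of escalating at a true DLT rate of 40%, and smaller if many stoppers are not followed. The rise from 31% to 46% applies only to a cohort that already contains one unexposed patient, so it should not be read as the average effect.

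The window problem for the staged variant does not depend on these assumptions: day 38 comes before day 42. Both points merit an amendment because the correction is cheap, with moderate confidence given the unknown stop rate.

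**What to change.** In Sections 10 and 16 and the synopsis:

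- Base the 3+3 counts on DLT-evaluable patients: any patient with a DLT, or one who received a pre-set minimum of the planned fractions and concurrent Sutent doses and completed the DLT window. The investigators should choose the thresholds. As an illustration, 75% of Sutent doses is 21 of 28, or 32 of 42 under the staged variant (0.75 × 42 = 31.5, rounded up). The fraction minimum need not be all ten.
- Replace, at the same level, patients who are non-evaluable for reasons other than treatment-related toxicity. State how under-exposure caused by toxicity short of a DLT is handled; this point does not ask for it to be scored automatically as a DLT.
- For patients on the staged variant, extend the DLT window to at least day 42.
- Keep all treated patients in the safety tables.

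**Cost.** Escalation is slightly slower. If all five levels open, phase I takes 15 to 30 patients. With 38 in phase II and 3 to 6 shared, the total is 15 + 38 − 3 = 50 to 30 + 38 − 6 = 62. Expected replacements are n × s/(1 − s): for 15 patients, 0.8 at 5% and 1.7 at 10%; for 30 patients, 1.6 and 3.3. That is about 1-3 extra, for a total of roughly 51 to 65. This may exceed the 52 planned on the synopsis page and reaches the top of the 50-65 anticipated in Section 16. If escalation stops early, all these numbers are smaller.
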